**6.6 Safety analysis**

Adverse events and their most serious reaction levels will be summarized in accordance with the standards of NCI CTCAE Version 5.0. Adverse events will also be summarized according to the severity of the event and its relationship with the study drug. The descriptive summary of laboratory test values ​​is mainly for outliers. Laboratory abnormalities will also be summarized according to the most severe level in NCI CTCAE Version 5.0.

**6.7 Plan of Statistical Analysis**

We will calculate the ORR and the 95% confidence interval. According to the type and severity of adverse events, we will list the number and rate of therapeutic adverse events. We use the Kaplan-Meier survival curve to describe the overall survival time (OS) and progression-free time (PFS) of the patients.

**7 Adverse event report and management**

**7.1 Definition of adverse events**

An adverse event (AE) is defined as any adverse medical event that occurs in the clinical trial subject from the signing of the informed consent form until 90 days after the last use of the study drug, regardless of whether there is a causal relationship with the study drug, it is judged as an adverse event. AE includes but is not limited to the following situations:

- Exacerbation of the original (before entering the clinical trial) medical condition/disease (including symptoms, signs, and exacerbations of abnormal laboratory tests);
- Any new adverse medical conditions (including symptoms, signs, newly diagnosed diseases);
- Abnormal laboratory test values ​​or results with clinical significance.

**7.2 Definition of serious adverse events**

Serious adverse events are those that meet at least one of the following criteria:

Causes death, except for deaths caused by disease progression of the research indication.

Life-threatening ("life-threatening" in the definition is an AE that is at risk of death when the subject occurs, and does not include AEs that may cause death if the event worsens).

Need to be hospitalized or extend the length of hospitalization, excluding the following situations:

-  Rehabilitation institutions
-  Nursing home
-  Admission to the routine emergency room
-  one-day surgery (such as outpatient/same-day/ambulatory surgery)
-  Hospitalization or prolongation of hospital stay unrelated to worsening AE is not SAE in itself. E.g: Hospital admission due to pre-existing diseases, no new adverse events, no exacerbations of pre-existing diseases (such as: to check the laboratory abnormalities that have persisted before the test); hospitalization for management reasons (such as: annual physical examination ); hospitalization specified in the trial protocol during the clinical trial (such as operation as required by the trial protocol); elective hospitalization that has nothing to do with worsening adverse events (such as elective surgery); scheduled treatment or surgery should be included in the entire trial protocol and / Or recorded in the subject's personal baseline data; admitted to the hospital only for the use of blood products.

 Cause permanent or severe disability/incapacity.

 Cause congenital abnormalities/birth defects.

Other important medical events: defined as events that harm subjects or require medical intervention to prevent any of the above from happening.

**7.3 Assessment of adverse events**

The investigator will evaluate all adverse events in accordance with NCI Common Adverse Events (CTCAE) version 5.0. Any adverse event that changes the CTCAE level will be recorded in the adverse event case report form/worksheet. All adverse events, regardless of the CTCAE grade, must be evaluated whether they are serious adverse events. For specific details, please refer to the table below.

Adverse event assessment rules

| **CTCAE**  **Grade** | **Level 1** | **Mild; asymptomatic or mild; only clinical or diagnostic manifestations; no intervention required** |
| --- | --- | --- |
|  | **Level 2** | **Moderate; requires minimal, partial or non-invasive intervention; restricts daily activities of the appropriate age** |
|  | **Level 3** | **Severe or important medical events require medication, but they are not immediately life-threatening; hospitalization or extended hospitalization; disability; limitation of self-care ability ADL** |
|  | **Level 4** | **Life-threatening consequences; urgent intervention required** |
|  | **Level 5** | **AE-related deaths** |
| **Severity** | A serious adverse event is any of the following adverse events that occur at any dose or during any use of the study drug: | |
|  | †Causes **death;** | |
|  | †Life **threatening; or** in the eyes of the researcher, the occurrence of the event puts the subject at immediate risk of death (Note: This does not include adverse events that may lead to death if they occur in a more serious form); | |
|  | †Causes **permanent or severe disability/dysfunction; (seriously interferes with the** ability to carry on a normal life); | |
|  | †Causes **or prolongs existing hospitalization; (Hospitalization** is defined as a hospitalization, regardless of the length of hospitalization, even if the hospitalization is only a preventive measure for continued observation. Note: Hospitalization [including hospitalization due to elective surgery] due to an existing disease that did not worsen during the study period does not constitute a serious adverse event. Pre-existing diseases refer to clinical diseases that were diagnosed before the use of study drugs and recorded in the patient's medical history); | |
|  | †Congenital **abnormalities/birth defects; (the offspring of** subjects who use the product, regardless of the time of diagnosis); | |
|  | **Other important medical events;** although it will not lead to death, life-threatening, or hospitalization, based on appropriate medical judgment, the event may endanger the subject and may require medical or surgical intervention to prevent the previously listed ( One of the outcomes marked as †) above, such an event can also be regarded as a serious adverse event. | |
| **duration** | Record the start and end date of the adverse event. If it is less than 1 day, indicate the appropriate length of time and unit. | |
| **Take measures** | Did the adverse event lead to the discontinuation of the study drug? | |
| **Relationship with study drug** | Did the study drug cause the adverse event? A medically qualified investigator needs to provide a causal evaluation result between the study drug and the adverse event. The investigator signs the original document or worksheet with the date (initial acronym) to support the causality evaluation on the AE form to ensure that a medically qualified causality evaluation is performed. This signed document must be kept within the required regulatory time frame. The purpose of the following standards is to serve as a reference guide to assist investigators in assessing the relationship between trial drugs and adverse events based on existing information.  **The following elements are used to evaluate the relationship between study drugs** and AEs; the greater the correlation between the items and their corresponding elements (in terms of quantity and/or intensity), the greater the likelihood that the study drug will cause adverse events; | |
|  | **Exposure** | Whether there is evidence that the subject is actually exposed to the test drug, such as: a true and credible past medical history, acceptable compliance assessment (drug count, log, etc.), expected pharmacological effects, drug/metabolite measurement in samples collected in vivo ? |
|  | **Time** | Is there a reasonable time sequence between adverse events and trial drug treatment?  Does the timing of the adverse event coincide with the drug-induced adverse event? |
|  | **Possible reason** | Whether the adverse event cannot be explained by other causes, such as underlying diseases, other drugs/vaccines, or other host or environmental factors |
|  | **Deprovocation test** | Is the study drug discontinued or reducing the dose/exposure/frequency?  If yes, can the AE be cured or improved?  If it is, it means that the deprovocation test is positive. If not, it means that the deprovocation test is negative.  Note: This standard does not apply if the following conditions occur: (1) An adverse event causes death or permanent disability; (2) The AE is cured/improved despite the continued use of the study drug; (3) The trial is a single dose trial; (4) The study drug has been used only once. |
|  | **Re-provocation test** | Is the subject repeatedly exposed to the study drug in this trial?  If yes, is the AE recurring or worsening?  If it is, then the provocation test is positive. If not, then the provocation test is negative.  Note: This criterion does not apply if the following conditions occur: (1) the initial AE resulted in death or permanent disability, or (2) the trial was a single-dose trial, or (3) the study drug was used only once.  Note: If a re-provocation test is planned for serious adverse events that may be caused by the test drug, or if the test drug is re-exposed, it may cause serious potential risks to the subject/patient. In this case, a re-provocation test is not recommended Unless it is considered that the continued medication may be beneficial to the patient and there is no alternative treatment available, it can only be carried out after obtaining the approval of the sponsor in advance. |
|  | **Consistency with experimental treatment characteristics** | Are the clinical/pathological manifestations of the adverse event consistent with the previous treatment data on the investigational drug or the pharmacology and toxicology trials of such drugs? |
| A medically qualified researcher will report the evaluation results of the relationship in the case report form/worksheet based on his/her best clinical judgment, including considering the relationship between the above factors. | | |
| **Record causality** | | **The following table can be used for causal association assessment (not all criteria need to be met)** |
| **related** | | There is evidence of exposure to study drugs. The time sequence of AE occurrence and study drug administration is reasonable. Compared with other causes, AEs are more likely to be explained by the study drug than other causes. |
| **Irrelevant** | | The subject did not use the study drug or the time relationship between the administration of the study drug and the occurrence of the AE is unreasonable or there are other reasons that are more likely to explain the adverse event, rather than the study drug (also applicable to overdose but no related adverse events Subject). |

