In summary, the combined application of SBRT, sintilimab, and GM-CSF may enhance the effect of immunotherapy, thereby improving the clinical efficacy in advanced NSCLC. So far, there have been no prospective studies to confirm this scientific hypothesis, as well as the clinical value of the combination therapy. Therefore, we plan to carry out a phase II study of SBRT combined with sintilimab and GM-CSF in the treatment of advanced NSCLC, attempting to explore the feasibility of this triple therapy which mechanically could enhance anti-tumor immune response through promotion of both innate and adaptive immune processes.

1. Study objectives

To explore the safety and preliminary efficacy of SBRT combined with sintilimab and GM-CSF in stage IV NSCLC patients without driver mutations such as EGFR, ALK, and ROS1.

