**2.2 Secondary objectives:**

**Treatment-related adverse events (TRAEs):** The proportion of the treatment-related toxic reactions in the total evaluable cases according to the Common Terminology Criteria Adverse Events (CTCAE) 5.0.

**Out-of-field (abscopal) response rate (ASR):** At any time through enrollment to last follow-up, the longest diameter of any un-irradiated target lesions (per RECIST v1.1) reduce ≥30% will be considered as out-of-field (abscopal) response. The ASR is defined as the proportion of patients with an out-of-field response in the total evaluable patients.

**Overall survival (OS):** The time interval from enrollment to death due to any cause. Patients who are still alive at the time of analysis will be censored at the date of last contact.

**Progression free survival (PFS):** The time interval from enrollment to the first documented disease progression or death due to any cause. Patients who are still alive without disease progression at the time of analysis will be censored at the last date of last radiographic follow-up.

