4. Height measurement is only performed during the screening period. Weight of subjects is measured before each administration. If the weight of the subject fluctuates less than 10% from the baseline (the day of the first study dose), the baseline weight is used to calculate the dose of chemotherapeutic drugs. Otherwise, the actual dose is calculated according to the body weight on the day of the planned administration.
5. Medical history must include medical and surgical history, history of smoking/alcohol consumption/family history, previous radiotherapy and chemotherapy, and symptoms of intracranial hypertension.
6. Blood routine includes red blood cell count (RBC), hemoglobin (Hb), white blood cell count (WBC), and white blood cell count (absolute neutrophil count and absolute lymphocyte count are required), hematocrit (HCT), platelets (PL).
7. Coagulation functions include PT and INR. It is carried out within 28 days before the first study dose during the screening period and during the safety follow-up. The lab tests are carried out in various research centers.
8. Blood biochemistry includes blood electrolytes (K, Na, Ca, Mg, Cl, HCO_3_^-^ are required), ALT, AST, γ-GT, total bilirubin, direct bilirubin, amylase, lipase, creatinine, urea nitrogen, serum albumin, blood glucose.
9. Thyroid function includes T3, T4, fT3, fT3, TSH.
10. Women of child-bearing age should undergo a urine or serum pregnancy test within 28 days before the first dose in the screening period. If the urine pregnancy test result cannot be confirmed as negative, a serum pregnancy test should be performed, and the serum pregnancy result shall prevail. Tests will be carried out in various research centers.
11. Urinalysis must include urine specific gravity (SG), urobilinogen (URO), occult blood (BLD), white blood cells (WBC), urine protein (PRO), urine glucose (GLU), bilirubin (BIL), ketone bodies (KET), urine red blood cells (RBC), urine color (COL).
12. The assessments of AE and laboratory test safety are evaluated according to CTCAE v 5.0. Definition, recording, relevance judgments, severity judgments, reporting time limits and management of AE and SAE are described in sections 5 and 7 of the protocol.

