
**5.2.8 Drug management**

5.2.8.1 Drug management

The investigational drug in this study is Sintilimab (IBI308). Sintilimab should be refrigerated at 2～8℃, protected from light, and stored in a dry place. Do not freeze. All test drugs are transported to each research center in the cold chain, and should be kept and distributed by special personnel. Test drugs should be stored in a refrigerator that only authorized personnel can open. After receiving the drugs, the investigator should confirm that the drug transportation temperature is within the specified range, sign for receipt after verification, and store at the specified temperature. If the temperature is abnormal during transportation or storage in the research center, the drug should be transferred to the specified temperature as soon as possible, and the subject should not be used for the time being, and reported to in time, and deal with it according to Innovent Biologics’ opinion. All experimental drugs provided by the sponsor can only be used in this experimental study, and shall not be used for purposes other than those specified in this protocol. The investigator must promise not to provide the trial drug to anyone unrelated to the trial. Sintilimab that has been discontinued due to special reasons should be stored under the same storage conditions until the inspector has completed the inventory and check, and arrange for recycling.

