**6.5.2 Secondary endpoint**

**Treatment-related adverse events (TRAE):** Treatment-related toxic reactions according to the CTCAE 5.0.

**Out-of-field (abscopal) response rate (ASR):** Out-of-field response was defined as reduced by ≥30% of the longest diameter from baseline in any un-irradiated RECIST1.1 evaluable target lesions. ASR was defined as the percentage of patients achieving out-of-field response.

**Overall survival (OS):** The time interval from the first day of enrollment to death from any cause. Patients who are still alive at the time of analysis will be censored by the date of last contact until cut-off date. The Kaplan-Meier method will be used to estimate the survival curves of the two groups, and the median OS (90% two-sided confidence interval) will be calculated.

**Progression free survival (PFS):** The time interval from enrollment to the first documentation of disease progression or death due to any cause. Patients who are still alive without disease progression until data cut-off will be censored by the time of the most recent radiographic follow-up. The Kaplan-Meier method was used to estimate the survival curves of the two groups, and the median PFS (90% two-sided confidence interval) was calculated.

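### Causality is judged against the study drug, so non-serious SBRT toxicity has no related category and can be left out of the TRAE rate for the triple combination

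*Protocol*

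**What the plan says.** The study objectives give the aim as "To explore the safety and preliminary efficacy of SBRT combined with sintilimab and GM-CSF in stage IV NSCLC patients". Section 2.2 makes TRAEs a secondary objective, measured as "The proportion of the treatment-related toxic reactions in the total evaluable cases", and section 6.5.2 gives the endpoint as "Treatment-related toxic reactions according to the CTCAE 5.0". Neither limits treatment to a drug.

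Note 12 to Table 1 says where relatedness is settled: "Definition, recording, relevance judgments, severity judgments, reporting time limits and management of AE and SAE are described in sections 5 and 7 of the protocol".

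Section 7.3 then puts one causality question for every event, whether the study drug caused it, and offers two answers. *Related* lists exposure to the study drug, reasonable timing and the deciding comparison: "Compared with other causes, AEs are more likely to be explained by the study drug than other causes". *Irrelevant* has three alternative grounds. The first two, no drug use and unreasonable timing, are in the clause that opens "The subject did not use the study drug or the time relationship between the administration of the study drug and the occurrence of the AE". The third is that some other reason explains the event better than the study drug does.

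The event record in section 7.4.3 also asks for the relationship to the study drug, and section 6.6 plans that "Adverse events will also be summarized according to the severity of the event and its relationship with the study drug". Section 5.2.8.1 states: "The investigational drug in this study is Sintilimab (IBI308".

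**The concern.** The endpoint is about the toxicity of a three-part treatment, one part of which is radiation. The rule that sorts events into related and irrelevant asks about a drug. Under that rule SBRT counts as another cause, and the more clearly an event is due to SBRT, the more firmly the rule points to irrelevant.

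TRAE is the only named safety endpoint of a single-arm trial, so there is no control rate against which an understated figure would show up. Overlapping toxicity is the most exposed. Section 5.2.2 lists pneumonitis as a sintilimab reaction and Table 2 lists pneumonia as a lung toxicity of SBRT. This is where the combination raises the safety question, and where attribution to a single agent is hardest.

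**Working it through.** No figure in the protocol depends on this point, so there is none to reproduce. The check applies the rule to the events it will meet.

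1. **Event before the first drug dose.** Table 1 schedules an adverse event assessment in the SBRT column, at the end of SBRT or before the d1 administration. No drug has been given, so the first ground for irrelevant applies. The length of this window is itself inconsistent: section 5 allows drug treatment to begin within two weeks after SBRT, while sections 5.2 and 5.3 start it on the second day after SBRT. Those sections must be reconciled. The point does not depend on the outcome, because the SBRT days themselves precede any drug on either wording.

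2. **Non-serious event after d1, attributed mainly to radiation**, such as inflammation within the irradiated field. The third ground applies, because another cause is likelier than the study drug. The event record in 7.4.3 holds no other attribution for a non-serious event.

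3. **Serious event.** Section 7.4.3 adds a causality evaluation of the research process and of other drugs. Section 7.4.1 refers to drug or procedure for serious events later than 90 days after the last dose. Serious events are therefore partly covered, but not consistently. Section 7.5 covers the same late events by relationship to the study drug alone. The paragraph on new anti-tumor treatment in 7.4.3 limits recording to serious events related to the study drug.

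4. **Wider wording elsewhere.** An exception under Table 3 in section 5.2.2 recognises treatment-related events that are unrelated to sintilimab. DLT item (3) in section 6.2 refers to the trial treatment. Section 6.7 lists therapeutic adverse events without a drug limit. These show that the protocol means more by treatment than 7.3 does by study drug. None gives a non-serious event an SBRT attribution or alters the two-way rule.

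5. **Size.** Read the TRAE rate per patient. A patient leaves the numerator only if toxicity attributed to SBRT was that patient's sole treatment-related toxicity. Let s be the share of such patients and n the number of patients. Then:

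   fall in the rate = 100 × s percentage points; patients lost = s × n

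   The protocol gives no value for s, so the values below are assumptions. Section 6.1 gives n = 56 eligible and 63 enrolled.

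| s (assumed) | Fall in rate | s × 56 | s × 63 |
|---|---|---|---|
| 0.02 | 2 points | 1.1 | 1.3 |
| 0.05 | 5 points | 2.8 | 3.2 |
| 0.10 | 10 points | 5.6 | 6.3 |
| 0.20 | 20 points | 11.2 | 12.6 |

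The direction does not depend on s. Compared with a TRAE defined as related to any component, a drug-only rule can remove events but not add them. In a rate for one type of event, the loss is not offset by an unrelated drug reaction in the same patient.

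**The case against.** The strongest reply is that the link from 7.3 to the TRAE rate is inferred. The endpoint says treatment-related, and no sentence equates a TRAE with a related code under 7.3. Section 7.3 describes its criteria as a reference guide, says that not all need be met, and leaves the answer to clinical judgment. Its examples of alternative causes are underlying disease, other drugs or vaccines, and host or environmental factors; protocol SBRT is not named. A sensible investigator could call a radiation reaction treatment-related. All this stands, and it rules out four stronger readings that a reader might infer.

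- *SBRT toxicity is certain to drop out.* It is not. The documents support a rule that leads there if followed as written, and scope for sites to differ if it is not.
- *The TRAE rate describes sintilimab alone.* This is not established. The naming of sintilimab in 5.2.8.1 is in a storage and supply clause, 7.3 also uses the plural for study and trial drugs, and 5.3 has its own table of GM-CSF reactions. Whether GM-CSF counts as study drug is unclear; only SBRT is excluded on every reading.
- *The safety data are lost or the run-in is compromised.* In general neither follows. Events are collected from consent and summarised by worst grade. DLT items (1) and (2) state no attribution condition, and item (3) already uses the wider term. No decision rule uses the TRAE rate.
- *The bias is known to be large.* The documents give no SBRT toxicity rate. The drug reactions that sections 5.2.2 and 5.3 anticipate, such as cold-like symptoms with GM-CSF, may leave few patients with SBRT toxicity alone.

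What does not stand is the reply that an analysis plan could settle the matter. Relatedness is judged at the site. If the form follows 7.3 and 7.4.3, an SBRT attribution that was never recorded for a non-serious event cannot be recovered at analysis.

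**Conclusion.** The point holds as a mismatch between the endpoint and the rule that feeds it. For non-serious events attributed mainly to SBRT, the protocol states no route to a related classification. The consequence is a TRAE rate that is biased downward, inconsistent between sites, or both. The all-cause summaries limit the damage, and so does the partial cover for serious events.

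The size is unknown. The range of about 1 to 11 of 56 patients (up to about 13 of 63) rests on the assumed 2% to 20% and on a per-patient reading of the rate. Since the endpoint is secondary and descriptive and no stopping rule depends on it, this should be fixed but does not put the primary result in doubt.

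**What to change.** For causality in sections 7.3, 7.4.3 and 6.6, replace study drug with study treatment, defined as SBRT, sintilimab and GM-CSF. On the adverse event form, record relatedness separately for each component. In sections 2.2 and 6.5.2, define a TRAE as an adverse event related to at least one component.

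Keep the existing more-likely threshold, but compare each component with causes outside the protocol treatment, so that one component is not a competing cause that clears another. A move to a cannot-be-excluded threshold would be a separate change and is not needed here.

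Use the same term for related serious events in section 7.4.1, in the new anti-tumor treatment paragraph of 7.4.3, and in section 7.5.

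The cost is protocol wording, extra tick-boxes on the form, slightly more data entry, and possibly a higher reported TRAE rate.
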